### Statistical analyses

#### Primary outcome variables

First, we will examine individual response patterns by means of (interrupted) time series analysis (ITS) to detect time trends in the amount of pleasure experienced during the study, and differences in the level and slope between pre- and post-intervention pleasure levels. Interrupted time series analysis is particularly useful to test changes in outcome rates in time periods before and after implementation of an intervention designed to change the outcome (see, for instance, [53]). The number of individuals who show a significant improvement in pleasure in the second month of the study period as compared to the first one will be compared across the three intervention groups to assess to what extent this improvement, if any, is likely to be due to spontaneous recovery or the mere daily registration of pleasure and activities, to the personalized lifestyle advice, or to the tandem skydive experience. In addition, we will explore whether changes in pleasure scores from pre- to post-intervention differ between the three intervention groups in a multilevel model. We will compare both (a) individuals who did and did not receive lifestyle advice; and, within the group who received lifestyle advice, (b) individuals who did and did not perform a skydive. We will use a multilevel model with two levels, in which Level 1 represents the momentary assessments, and Level 2 the individual level (e.g., intervention group). The main advantage of multilevel analyses is that it takes the nested structure of the data into account. By conducting multilevel analyses, we will be able to compare post-intervention mean levels of momentary pleasure between the three intervention groups, while controlling for the level of pleasure in the pre-intervention period (i.e., the observation month).

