## Methods

### Participants

For the screening survey, 2000 young adults (18–24 years old) will be recruited from the general population. Inclusion criteria for the survey are age between 18–24 years and sufficient knowledge of the Dutch language. Inclusion criteria for the anhedonia group are (a) persistent pleasure loss and (b) willingness to perform a skydive. For the non-anhedonic control group, the inclusion criteria are (a) no loss of pleasure and (b) willingness to perform a skydive. Exclusion criteria are inability to keep an electronic diary three times a day; current professional treatment for psychiatric problems; current use of psychotropic medication; epilepsy; pregnancy; conditions that make it impossible to be attached to the tandem master (e.g., loose prostheses); height of more than 2 m; weight of more than 95 kg; inability to raise one’s legs 90° (needed for safe landing after tandem skydive); significant visual or hearing impairments; experience with skydiving, bungee jumping, base jumping, or skyjumping; cardiovascular complaints/problems. All criteria were included as questions in the screening survey.

We will use three questions from the Domains and Dimensions of Pleasure Scale ​(DDOPS; [name], [name], [name], [name], [name], & [name]: Domains and Dimensions of Pleasure Scale (DDOPS): a novel questionnaire to assess anhedonia, submitted) to measure persistent loss of pleasure. These questions assess the level of pleasure experienced during the past two weeks, whether this level represents a loss compared to what is considered normal to that person, and the duration of the loss. Participants who report low pleasure levels (score below the 25th percentile), a loss compared to normally experienced pleasure levels, and a minimum duration of the loss of 2 months are eligible for inclusion. We aim to complete the data collection in at least 60 anhedonic persons (20 in each condition). Because we expect some dropout during the data collection, we decided to select 24 individuals for each condition (72 in total). The non-anhedonic control group will consist of 60 individuals.

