#### Momentary questionnaires

The items for the momentary questionnaires are presented in Table 2. Pleasure is the primary outcome measure. The other momentary items relate to secondary outcome variables.

**Table 2 Tab2:** Description of Momentary Questionnaire

Question	Dutch	Translation	Response range	Range	Description
1.	Ik probeerde in slaap te vallen om…	I tried to fall asleep at…	Hours - minutes	n/a	Time of trying to sleep
2.	Aantal minuten totdat ik in slaap viel	Number of minutes until falling asleep	Number of minutes	n/a	Time until falling asleep
3.	Ik werd wakker om…	I woke up at…	Hours - minutes	n/a	Time of waking up
4.	Hoeveel keer werd ik wakker gedurende de nacht?	How many times did I wake up during the night?	0, 1, 2, 3, 4, 5 or more	0–5	Frequency of awakenings
5.	Totaal aantal minuten wakker geweest	Total number of minutes awake	Number of minutes		Time of awakenings
6.	Mijn slaapkwaliteit was	My sleep quality was	“Very bad” to “Very good”	0–100	Sleep quality
7.	Ik heb vervelend gedroomd	I had bad dreams	“Not at all” to “Very much”	0–100	Nightmares
8.	Ik voelde me uitgerust bij het wakker worden	I felt rested when I woke up	“Not at all” to “Very much”	0–100	Rest
9.	Ik ben nu…	I am now…	(1) Home (2) Work/school (3) On the way (4) Restaurant/café (5) In nature (6) Vacation home/hotel/camping (7) Hospital/care facility (8) Shop (9) Gym/sports club (10) Somewhere else	1–10	Current location (only one box could be checked)
10.	Ik ben nu…	I am now…	(1) Alone (2) With partner (3) With family (4) With friends (5) With fellow students (6) With colleagues (7) With acquaintances (8) With strangers	1–8	Current social context (multiple answers possible)
11.	Ik voel me nu plezierig	I feel pleasurable	“Not at all” to “Very much”	0–100	Current pleasure
12.	Ik voelde me geïnteresseerd in de dingen om me heen	I felt interested in the things around me	“Not at all” to “Very much”	0–100	Positive affect, low arousal
13.	Ik voelde me overstuur	I felt upset	“Not at all” to “Very much”	0–100	Negative affect, high arousal
14.	Ik voelde me opgewekt	I felt joyful	“Not at all” to “Very much”	0–100	Positive affect, high arousal
15.	Ik voelde me somber	I felt gloomy	“Not at all” to “Very much”	0–100	Negative affect, low arousal
16.	Ik voelde me daadkrachtig	I felt determined	“Not at all” to “Very much”	0–100	Positive affect, high arousal
17.	Ik was niet vooruit te branden	I felt sluggish	“Not at all” to “Very much”	0–100	Negative affect, low arousal

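### The first-listed primary analysis compares counts of individually significant improvers between arms of 20 to 24, at a substantial cost in power, and no analysis is named as decisive

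*Protocol article*

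**What the plan says.** The Momentary questionnaires section states: "Pleasure is the primary outcome measure". The section Primary outcome variables then sets the order of analysis. It opens: "First, we will examine individual response patterns by means of (interrupted) time series analysis (ITS"), looking for trends and for "differences in the level and slope between pre- and post-intervention pleasure levels". The between-arm step follows: "The number of individuals who show a significant improvement in pleasure in the second month", relative to the first month, is to be compared across the three groups. From that comparison the protocol intends to judge how far improvement is due to spontaneous recovery or mere registration, to the advice, or to the skydive.

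The analysis that keeps the size of each change comes after: "In addition, we will explore whether changes in pleasure scores from pre- to post-intervention differ between the three intervention groups in a multilevel model". It compares month-2 means adjusted for the observation month, with two contrasts: advice against no advice and, among those advised, skydive against no skydive.

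On numbers, the Participants section says "We aim to complete the data collection in at least 60 anhedonic persons (20 in each condition") and "we decided to select 24 individuals for each condition (72 in total"). The Sample size calculation section presents the individual series and the multilevel model as two approaches to the main question. For the first it compares at least 90 observations before and after the intervention with a recommended minimum of 12, and foresees no power problem. It gives no power for the comparison of counts.

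**The concern.** Reducing each person to significant or not significant has two consequences.

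First, significance is not the same as improvement. The shift a person needs in order to count scales with that person's own diary variability and grows with autocorrelation. Two people with the same gain can be classified differently.

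Second, the comparison between arms then rests on 20 to 24 yes/no values per arm. The 90 diary entries per month sharpen each individual test, but they do not add units to the comparison of arms.

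The attribution to recovery, advice or skydive is tied to this weaker statistic. If the counts show no difference and the multilevel model does, the protocol does not say which result answers the main question.

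**Working it through.** **The plan's own figure.** The only calculated group size is 21 per group, for the monthly questionnaires (d = 0.8, correlation 0.6, power 0.8, alpha 0.05, two-sided assumed). With variance factor 2(1 − 0.6) = 0.8, the effective difference is 0.8/√0.8 = 0.894. The normal approximation gives n = 2(1.96 + 0.84)²/0.8 = 19.6, so 20; the t-based answer is 21 (power 0.807). The figure reproduces, but it does not concern the counts.

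**Assumptions for momentary pleasure (none is in the document).** 90 + 90 entries per person; AR(1) autocorrelation 0.3; SD of true individual change 0.5 and arm difference 0.5, both in within-person SDs; a person counts if the shift is positive and significant at two-sided 5%. The document names no test for the counts, so Fisher and uncorrected chi-square are both shown. Comparisons are between two arms, without multiplicity adjustment.

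**Step 1, the individual threshold.** The SE of a month-to-month shift is √[2 × (1.3/0.7)/90] = 0.203 within-person SDs. The smallest significant shift is 1.96 × 0.203 = 0.398 SDs. On the 0–100 item that is about 4 points for a diary SD of 10 and about 10 points for a diary SD of 25. A 6-point gain counts for the first person and not for the second.

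**Step 2, improver rates.** The SD of the estimated change is √(0.5² + 0.203²) = 0.540.
- Control: P(Z > 0.398/0.540) = P(Z > 0.74) = 23%.
- Treated: P(Z > (0.398 − 0.5)/0.540) = P(Z > −0.19) = 57%.

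**Step 3, power at 20 per arm.** Exact binomial power for 23% against 57% is 0.49 (Fisher) or 0.61 (chi-square). A t-test on the same changes has standardised difference 0.5/0.540 = 0.93 and power 0.81. Simulation that also lets diary SDs vary between people (lognormal, log-SD 0.3) gives slightly lower values:

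| Per arm | Fisher | Chi-square | t-test on changes |
|---|---|---|---|
| 20 | 0.47 | 0.59 | 0.80 |
| 24 | 0.58 | 0.70 | 0.87 |

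**Step 4, if people are classified on the level term of a level-and-slope model.** The SE of the level change is 0.395, about twice 0.20. Power for counts at 20 per arm falls to 0.27 (Fisher) or 0.39 (chi-square).

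**Step 5, a second route.** Borrow d = 0.8 from the questionnaire calculation, apply it to individual change, and cut the distribution at control improver rates of 5% to 50% (assumed).

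| Per arm | Fisher | Chi-square | t-test on changes |
|---|---|---|---|
| 20 | 0.17–0.37 | 0.29–0.49 | 0.69 |
| 24 | 0.23–0.50 | 0.36–0.62 | 0.77 |

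By normal approximation, 80% power needs 40 to 76 per arm for counts against 25 for changes. The loss appears in every setting checked.

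**The case against.** The strongest reply is that the efficient model is already planned. The sample size section lists it as one of two approaches to the main question and claims sufficient power for it. The study calls itself exploratory, and individual response is a deliberate target that a mean contrast does not address. The counts are only said to be compared, with no formal test named. All of this stands, and it makes the remedy small. It does not remove the problem: the count comes first, it carries the attribution, the multilevel model is introduced as an addition, and no order of authority is given. The objectives also describe a superiority randomised trial, and the Discussion states directional hypotheses.

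Three stronger readings are tempting and are not supported.

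- **That the trial discards effect sizes.** Only the count comparison does; the multilevel model keeps them.
- **That the count comparison will usually miss an effect the same data can show.** Among simulated trials in which the t-test was significant, the count test was also significant in 58% (Fisher) or 70% (chi-square) at 20 per arm, and in 67% or 78% at 24. Only classification on the segmented level term brings this to around or below half (31% or 46% at 20; 38% or 51% at 24). The document's month-2 against month-1 wording reads at least as naturally as a simple shift.
- **That arm differences in diary completion would materially change the counts.** The Missing data section requires 80% completion each month. Going from 100% to 80% moves the SE from 0.201 to 0.213 and, with no treatment effect and a true-change SD of 0.5, the improver rate from 23.2% to 22.1%. That is about 0.2 of a person in 20.

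**Conclusion.** The concern holds in a limited form. The first-listed between-arm analysis of the primary outcome is clearly weaker than one already in the plan, and the plan does not say which decides. Under the stated assumptions, power falls from 0.80 to about 0.47–0.59 at 20 per arm and from 0.87 to about 0.58–0.70 at 24. It falls further, to 0.27–0.39 at 20 per arm, if people are classified on the level term of a segmented model. The exact sizes depend on the assumed autocorrelation, SD of change, arm difference and count test. The direction did not change in any setting examined. Pooling both advice arms against no intervention would raise power for both methods.

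**What to change.** State that the multilevel contrast carries the between-arm inference: month-2 pleasure adjusted for the month-1 level, by assigned arm, with the stratification factor sex in the model. Attach the attribution to recovery or registration, advice or skydive to that contrast. Keep the individual time series as planned, and report the number of improvers per arm descriptively with confidence intervals.

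The cost is wording: no new data and no new models are needed. What is given up is a formal test on the number of improvers, which is the easiest result to communicate.

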**Fig. 1 Fig1:**
[figure not shown]
Flowchart of the study design

After the pre-intervention observation month, the anhedonic participants will be randomly assigned (stratified on gender) to: (1) no intervention; (2) personalized lifestyle advice, based on association patterns observed in the first month; or (3) personalized lifestyle advice followed by a tandem skydive. After the second month, at the start of the third month, all participants are free to choose whatever they prefer, regardless of the intervention received after the first month: no intervention, lifestyle advice, or lifestyle advice and a tandem skydive. This last month is added to provide a more realistic impression of the feasibility and appeal of the interventions.

Before and after each observation/intervention month as well as after 6 months and one year (in total 6 times), the participants in the anhedonic groups will fill out an online questionnaire. We will collect blood samples along with the monthly and follow-up questionnaires, i.e. six times per person in total. Before and after their first skydive, participants will be asked to donate a total of four saliva samples. Saliva will be collected by means of salivettes, on which the participant has to chew. A member of the research team will provide the salivettes to the participants and provide instructions on how to use them. The salivettes will be collected by the same research member and transported to the UMCG lab.

The anhedonic intervention groups receive 75 Euro after the observation month; another 125 Euro after the first intervention month; and 200 Euro after the second intervention month. They will receive these incentives only if they reach the required compliance rate of 80% within the required time frame, if they fill out all monthly assessments and provide the required blood samples. For the two follow-up measurements they will receive 50 Euro per measurement, once assessments are filled out and blood samples are provided. This means that anhedonic participants will receive up to 500 Euro in total.

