### Randomization

Stratified by gender by means of a block randomisation procedure, participants will be randomly assigned to: (1) no intervention; (2) personalized lifestyle advice; or (3) personalized lifestyle advice followed by a tandem skydive. For males and females separately, a block size with an allocation sequence of six will be used with an equal condition distribution (i.e. each condition is present twice in a block of six). A total of 12 blocks will be created by one of the team members (MM), using an online randomisation program. The allocation will be done by other team members (i.e., ER, CV, or VH) than the one who created the allocation sequence. As it will be clear to participants which intervention they will receive, intervention allocation cannot be blinded to participants nor to the research team.

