#### Tandem skydive

A tandem skydive is a skydive from an airplane during which the participant is securely attached to a trained tandem master. The tandem skydives will be performed from airport Hoogeveen at Skydive association Eelde-Hoogeveen. Participants do not need an extensive training; a brief instruction suffices. When they arrive at airport Hoogeveen they will first receive a brief instruction on how to keep their body in the air and how to land. Skydives will be made from an altitude of three kilometres. Landing will be in a sitting position on grass. If it turns out that participants categorically decline the tandem skydive, an alternative thrill experience will be offered. Alternatives are the ‘Skydiver’ or the ‘Goliath’, both attractions in a Dutch amusement park (i.e., Walibi Holland) that offer free fall experiences.

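### The multilevel skydive contrast is worded by who jumped while the text around it speaks of the randomised groups; if anyone assigned to the skydive declines, the two wordings give different analyses

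*Protocol article*

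**What the plan says.** All references are to the Protocol article.

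- *Procedure* and *Randomization*: after the observation month, "the anhedonic participants will be randomly assigned (stratified on gender") to no intervention, advice only, or advice plus skydive. Allocation is equal: "each condition is present twice in a block of six".
- *Participants*: on numbers, "we decided to select 24 individuals for each condition (72 in total"). On eligibility, "Inclusion criteria for the anhedonia group are (a) persistent pleasure loss and (b) willingness to perform a skydive".
- *Primary outcome variables*, general wording: the model explores whether changes in pleasure "differ between the three intervention groups in a multilevel model". Intervention group is given as the example of an individual-level variable, and the paragraph closes by comparing the three groups with adjustment for pleasure in the observation month.
- *Primary outcome variables*, specific contrasts: first "(a) individuals who did and did not receive lifestyle advice", then, "within the group who received lifestyle advice, (b) individuals who did and did not perform a skydive".
- *Tandem skydive*: "If it turns out that participants categorically decline the tandem skydive, an alternative thrill experience will be offered". The alternatives are two free-fall attractions in an amusement park. The analysis group of a person who takes one is not stated.

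No section says that participants are analysed in the arm to which they were assigned.

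**The concern.** The advice-only and advice-plus-skydive arms differ by randomisation in one respect, assignment to the skydive. A comparison of those two arms therefore answers the second primary objective without confounding. The specific contrast instead sorts people by something that happens after randomisation, whether they jumped. A person assigned to the skydive who received advice and then declined did not perform a skydive. On the literal wording that person is counted with the advice-only arm, even if a substitute ride was taken.

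Two things then go wrong together. The skydive group keeps only those who went through with it, and the comparator gains people selected for declining. If declining is related to later pleasure, the contrast mixes that relation with the effect of the skydive. A link is plausible on the document's own account: *Background* describes loss of drive in anhedonia and intense fear during a jump. The team is not blinded to allocation (*Randomization*), so the choice between two permitted readings should not be left until the data are in.

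**Working it through.** **The plan's own figure.** The document gives no calculation for this contrast. The nearest is 21 per group for the monthly questionnaires (*Sample size calculation*: d = 0.8, correlation 0.6, power 0.8, alpha 0.05, taken as two-sided). With variance factor 2(1 − 0.6) = 0.8, n = 2 × (1.960 + 0.842)² × 0.8 / 0.8² = 19.6, so 20 by the normal approximation and 21 by the noncentral t. The figure reproduces. The point does not depend on it.

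**Inputs for the check.** 24 per arm (*Participants*). The number of decliners k and the gap D are assumptions, because the document gives neither. D is how much lower decliners would score than jumpers under the same treatment. It is measured after adjustment for observation-month pleasure, in SDs of the adjusted per-person outcome.

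**Bias of the as-performed contrast with no true effect.** Set the jumpers' mean to 0.

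1. Jumpers: 24 − k people, mean 0.
2. Advice-only arm: 24 people. Randomisation gives it the same expected share k/24 of people who would have declined, so its expected sum is −kD.
3. Decliners moved across: k people, sum −kD.
4. Pooled non-jumpers: sum −2kD over 24 + k people.
5. Bias = 0 − [−2kD/(24 + k)] = **2kD/(24 + k)**.

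The rejection rate of a nominal two-sided 5% test uses the normal approximation with SE = √[1/(24 − k) + 1/(24 + k)].

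| k | Bias | D = 0.25 | D = 0.5 | D = 0.8 |
|---|---|---|---|---|
| 0 | 0 | 0; 5.0% | 0; 5.0% | 0; 5.0% |
| 2 | 0.154D | 0.04 SD; 5.2% | 0.08 SD; 5.8% | 0.12 SD; 7.1% |
| 4 | 0.286D | 0.07 SD; 5.7% | 0.14 SD; 7.8% | 0.23 SD; 12.2% |
| 6 | 0.400D | 0.10 SD; 6.3% | 0.20 SD; 10.3% | 0.32 SD; 18.9% |

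**Direction.** Suppose the substitute ride itself raises pleasure by E. The decliners' sum becomes −kD + kE, and the bias becomes (2kD − kE)/(24 + k). It turns against the skydive once E exceeds 2D, and also if D is negative.

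**As-randomised contrast.** Comparing 24 with 24 by assigned arm gives zero bias from this source, whatever k and D are. The cost is dilution. If jumpers gain 0.8 SD and decliners nothing, the arm difference is 0.8 × (1 − k/24): 0.80, 0.73, 0.67 and 0.60 SD for k = 0, 2, 4 and 6. With 24 per arm and the variance factor of 0.8 borrowed from the monthly-questionnaire calculation, power is 0.87, 0.81, 0.73 and 0.64.

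**The case against.** The strongest reply is that the clause is shorthand. The sentences on both sides of it refer to intervention groups, which the document defines by assignment. The two contrasts are also the natural pair for a three-arm factor: both advice arms against none, then skydive against advice only. No sentence moves decliners into the comparator, and offering them another free-fall experience fits at least as well with keeping them in the skydive arm. Refusal is mentioned only conditionally, and willingness to jump is an inclusion criterion. The model adjusts for earlier pleasure, which removes part of any gap. Finally, the handling of non-adherers is often left to an analysis plan.

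Much of this stands. A reader might infer that the plan is plainly an as-treated analysis and that randomisation is given up for the skydive question as a whole. The document does not support that: the paragraph is inconsistent rather than clearly as-treated, and the count of individual improvers is compared across the three groups. The reply does not remove the conflict, however. The clause states a grouping rule that differs from the sentences around it, so this is not detail left for later. The willingness criterion makes refusals less likely, but the protocol still provides for them.

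**Conclusion.** The point holds as a conflict within the stated primary-outcome analysis, limited to the multilevel skydive contrast. Followed literally, the clause replaces a randomised comparison with one defined by behaviour after randomisation. Followed by its surroundings, it does not. The size depends on k and D: at D = 0.5 SD, 0.08 SD with 2 decliners and 0.14 SD with 4, and nothing if all assigned participants jump.

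Three stronger conclusions are tempting but unsupported:

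- **That the bias favours the skydive.** This requires decliners to have the worse prognosis and the substitute ride to have little effect. The document establishes neither.
- **That the bias is large, for example with D = 1 SD.** Nothing in the document supplies such a gap, and the stated adjustment works against it. As an illustration, take a raw gap of 1 SD at both times and borrow the correlation of 0.6. Then 1 − 0.6 = 0.4 of a raw SD is left, which is 0.4/√(1 − 0.6²) = 0.5 in adjusted SDs.
- **That the advice contrast is biased too.** It has the same exposure wording, but nothing in the document foresees anyone in the two advice arms going without advice in month 2. Free choice begins only in month 3.

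**What to change.** In *Primary outcome variables*, state that contrast (b) compares all participants randomised to advice plus skydive with all randomised to advice only. People who decline the jump, including those given the alternative experience, remain in the advice-plus-skydive arm. Word contrast (a) by assigned arm as well, for consistency. Report any comparison by actual performance only as a labelled supplementary analysis, with the number of decliners shown.

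This takes a sentence or two, needs no new data and changes nothing in how participants are treated. It concerns only the arm in which a person is counted and leaves the separate 80% diary-completion rule in *Missing data* as it is. The cost is the dilution shown above: small with few decliners, and a fall from 0.80 to 0.60 SD if 6 of 24 decline and gain nothing. The estimate then describes the effect of being assigned to the skydive.

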**Methods:**

Our study design is an exploratory intervention study, preceded by a cross-sectional survey as a screening instrument. For the survey, 2000 young adults (18–24 years old) will be selected from the general population. Based on survey outcomes, 72 individuals (36 males and 36 females) with persistent anhedonia (i.e., more than two months) and 60 individuals (30 males and 30 females) without anhedonia (non-anhedonic control group) will be selected for the intervention study. The non-anhedonic control group will fill out momentary assessments of pleasure and lifestyle behaviors three times a day, for one month. The anhedonic individuals will fill out momentary assessments for three consecutive months. After the first month, the anhedonic individuals will be randomly assigned to (1) no intervention, (2) lifestyle advice only, (3) lifestyle advice plus tandem skydive. The personalized lifestyle advice is based on patterns observed in the first month.

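### The multilevel arm comparison names month-1 pleasure but not gender, the randomisation stratum; if gender is still prognostic, its reported standard error is mildly too wide

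*Protocol article*

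**What the plan says.** **Design.** The Randomization section of the protocol article opens: "Stratified by gender by means of a block randomisation procedure". Within each sex, "a block size with an allocation sequence of six will be used with an equal condition distribution", so each condition occurs twice per block. The Procedure section also states the stratification by gender, and no other stratification factor is named. The abstract plans for "72 individuals (36 males and 36 females) with persistent anhedonia". The Participants section aims for complete data in "at least 60 anhedonic persons (20 in each condition") and enrols more to allow for dropout: "we decided to select 24 individuals for each condition (72 in total").

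**Analysis.** Under Primary outcome variables, post-intervention momentary pleasure is compared between the three groups in a two-level model, "while controlling for the level of pleasure in the pre-intervention period (i.e., the observation month"). The person level is described only by example: "Level 2 the individual level (e.g., intervention group"). Neither the sample size section, the statistical analysis sections nor the Missing data section mentions gender for the between-arm comparisons.

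**The concern.** Analysis should normally follow randomisation: a factor used to balance the arms belongs in the model that compares them. Blocking within gender makes the male-female difference cancel out of the arm contrast. If the model has no gender term, the same difference stays in the residual variance, and the standard error is calculated as if gender had been left to chance. Confidence intervals are then wider than the design warrants, and the test rejects less often than its nominal level.

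The trial is small, with a target of 20 completers per arm, and the Strengths and limitations section concedes that subtle group differences may be missed. There is little reason to give up precision that the design has already provided.

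**Working it through.** **1. The plan's own figure.** The only sample size calculation with an effect size is for the monthly questionnaires: 21 per group for d = 0.8, correlation 0.6, power 0.8 and alpha 0.05 (two-sided assumed). With a change-score variance of 2(1 − 0.6) = 0.8, the normal approximation gives n = 2(1.960 + 0.842)² × 0.8 / 0.8² = 19.6, hence 20; the noncentral t calculation gives 21. The figure reproduces, but it does not concern the multilevel model. For that model the article gives no SD, standard error, effect size or gender effect.

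**2. Balance by design.** 12 blocks × 6 = 72 persons, so 6 blocks and 36 persons per sex. Two places per arm per block give 12 per arm per sex, or 24 per arm. Gender is then orthogonal to arm.

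**3. Excess in the reported standard error.** Let g be the male-female gap in month-2 pleasure after adjustment for month-1 pleasure, in units of the person-level residual SD. With a 1:1 split, omitting gender adds g²/4 to a residual variance of 1:

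- share of residual variance due to gender: R² = (g²/4) / (1 + g²/4)
- ratio of the standard error without gender to that with gender: √(1 + g²/4)
- with the degrees of freedom counted (intercept, two arm terms, baseline): √(1 + (g²/4) × N/(N − 4)), where N = 60 or 72

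For g = 0.5: g²/4 = 0.0625; √1.0625 = 1.031; with N = 60, √(1 + 0.0625 × 60/56) = 1.033.

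**4. Simulation check.** There were 24 persons per arm, balanced on gender, with 4,000 runs per gap. Person-level covariance analysis on arm and baseline was used, which is equivalent to a random-intercept model with balanced diaries. The contrast was skydive plus advice against advice alone. A month-1 to month-2 correlation of 0.6 was assumed; the ratio in step 3 does not depend on it.

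| g (assumed) | R² | Ratio, N = 60 | Ratio, N = 72 | Simulated ratio | Type I error without gender | Type I error with gender |
|---|---|---|---|---|---|---|
| 0 | 0% | 1.000 | 1.000 | 1.000 | 0.050 | 0.050 |
| 0.2 | 1.0% | 1.005 | 1.005 | 1.005 | 0.046 | 0.048 |
| 0.3 | 2.2% | 1.012 | 1.012 | 1.011 | 0.047 | 0.049 |
| 0.5 | 5.9% | 1.033 | 1.033 | 1.032 | 0.039 | 0.045 |
| 0.8 | 13.8% | 1.082 | 1.081 | 1.079 | 0.034 | 0.051 |

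The Monte Carlo error of a 5% rate is √(0.05 × 0.95 / 4000) = 0.0034. The drop in type I error is therefore clear only at gaps of 0.5 and 0.8.

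**5. What happens to the estimate itself.** In the model without gender, the actual SD of the simulated arm difference stayed between 0.228 and 0.234 across all gaps. The standard error that the model reported rose from 0.232 at g = 0 to 0.251 at g = 0.8. The estimate keeps the benefit of stratification; the reported standard error does not show it.

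**The case against.** The strongest reply is that the article does not exclude gender. The person level is introduced with an example, and the adjustment clause sits in a sentence about what multilevel analysis makes possible. A condensed article may leave the full covariate list to an analysis plan that is not shown. This stands as far as wording goes: the plan does not name gender, and a reader who infers that gender is deliberately left out goes beyond the text. It does not remove the point, because the article does state an adjustment, and that adjustment does not reflect the stratified design.

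The second reply is that the effect may be nil. That also stands. Month-1 pleasure is the same outcome averaged over a month, and it may absorb most of any gender difference. A flat statement that the standard error is too wide is not supported.

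Third, the error is on the safe side and the article calls this comparison exploratory. Both are true, and they keep the point minor.

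**Conclusion.** The point holds in conditional form and is minor. If gender remains prognostic after baseline adjustment, a model fitted with only the named covariate reports a standard error that is about 0.5 to 1% too wide at gaps of 0.2 to 0.3 SD, 3% at 0.5 SD and 8% at 0.8 SD. If gender is not prognostic, there is no excess. The gaps are assumptions; the article gives none. With arms balanced on gender there is no bias and no inflation of type I error. Exact balance is planned at randomisation but not guaranteed among those analysed, because the Missing data section excludes persons below 80% completion in any month, including the month after allocation.

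Three stronger readings are not supported:

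- **That stratification brings no precision.** The estimate does gain precision (step 5); only the reported standard error fails to credit it.
- **That a definite amount of power is lost.** The article gives no effect size for this model. Its d = 0.8 belongs to the questionnaires, and a 20 against 20 calculation would not describe the advice against no-advice contrast, which sets two arms against one.
- **That the comparison of improver counts and the questionnaire ANOVAs suffer equally.** Neither names gender, but no calculation was made for them.

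**What to change.** Under Primary outcome variables, state that the multilevel model for post-intervention pleasure includes gender as a Level 2 fixed effect alongside month-1 pleasure.

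This is one sentence of wording. Sex is already collected at screening and used for allocation, so no new data are needed. It uses one person-level degree of freedom (N − 4 becomes N − 5: 56 to 55 with 60 persons, 68 to 67 with 72). If gender turns out not to matter, almost nothing is lost: the simulated ratio of standard errors at no gap was 1.000.
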